### Sample size

According to the protocol, the patients will be randomly assigned into two groups, and they will all be evaluated (with NPRS) four more times after the baseline assessment (15 days, 4 weeks, 12 weeks, and 24 weeks, post-intervention). The main objective is to examine the possible diversity in NPRS (primary outcome) improvement among patients in different groups. The regular statistical approach to do this is to perform repeated measures ANOVA (rmANOVA), taking as given that all ANOVA assumptions are met (for example, normality of scores). Thus, the statistical power analysis for an rmANOVA procedure is as follows: we, as a priori, assume a number of groups equal to two and a number of measurements (except baseline) equal to four. More specifically, the NPRS is expected to be reduced in the two groups (CRYO and CRFA) at least 30%, relative to baseline assessment. According to Cohen [35], this fact denotes a medium effect size of approximately 0.50. Statistical significance is usually considered at the 5% level, and the power analysis curve for the rmANOVA is shown in Fig. 3. This figure illustrates that approximately 47 patients suffice for an achieved power of 80% using rmANOVA, taking into account a moderate effect size and 62 patients for 90% statistical power. Considering a 10% loss of follow up, we will enroll 70 patients in the study.

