### Statistical methods

The sample size and power in the study have been previously described. Another statistical approach for the study is to evaluate all follow-up (post-intervention) measurements separately from the baseline. This may occur in two possible ways: one with the use of an ANCOVA procedure and the other with the use of ANOVA on the difference in the scores (follow-up minus the baseline). As Borm et al. [36] suggested, the ANCOVA approach requires a significantly smaller number of participants, reduced by a multiplicative factor that depends on the correlation estimate between the prior and posterior scores, which is usually high. More specifically, a significance level of 5% along with a power of 80% is achieved with 24–45 patients in total, when the correlation estimates between the a priori and a posteriori score is approximately 80–90%, which is a realistic approach. To sum up with the statistical plan, longitudinal (that is, repeated measures) analysis will be conducted with repeated measures ANOVA. Furthermore, the slopes of the score trajectories (trendlines) will be compared among the two patient groups using 1-way ANOVA. Bivariate comparisons for baseline versus follow-up will be conducted using ANCOVA. 1-way ANOVA will assist in detecting variations in bivariate differences of scores (baseline versus each follow-up) among the two patient groups. Data will be reported as differences between group means (means ± standard deviations, 95% CIs) if normal distributed, otherwise as medians with interquartile ranges. Categorical data will be reported as numbers and proportions. A statistically significant difference of at least two in NPRS scores between groups, will be interpreted as a minimal clinically important difference (MCID). The statistical method of pairwise (available case analysis—ACA) deletion will be used for missing data at only one time point. If more than two time points are missed the list-wise (Complete-case analysis—CCA) deletion method will be used. Statistical analysis will be performed using R language and Rstudio IDE, two well-known open-source products.

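### Repeated measures ANOVA is adopted with its assumptions taken as met; if correlation falls with time between visits, an uncorrected group-by-time test would reject somewhat too often

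*Protocol article*

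**What the plan says.** Under Sample size, the aim is stated as a comparison between arms: "The main objective is to examine the possible diversity in NPRS (primary outcome) improvement among patients in different groups". Repeated measures ANOVA is chosen for it, "taking as given that all ANOVA assumptions are met (for example, normality of scores". The power calculation is told to "assume a number of groups equal to two and a number of measurements (except baseline) equal to four". It takes an effect size of 0.50 and a 5% level, and reads from a power curve that "approximately 47 patients suffice for an achieved power of 80% using rmANOVA" and "62 patients for 90% statistical power". Seventy are enrolled to allow for 10% loss.

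Under Statistical methods, the commitment is repeated: "longitudinal (that is, repeated measures) analysis will be conducted with repeated measures ANOVA". That section adds one-way ANOVA on individual slopes, ANCOVA of follow-up on baseline, and one-way ANOVA on change at each visit. It also calls a correlation of 80–90% between prior and posterior scores realistic. Neither section names the term that serves as the main test (group, time or group-by-time), and neither mentions sphericity.

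**The concern.** The univariate F test for a within-subject term has its nominal size only under sphericity. Unequal spacing of visits does not break that by itself; the covariance pattern decides. The visits here are 2, 8 and 12 weeks apart, however, and the Introduction expects cryoneurolysis-treated nerves to recover over time. If patients recover at different rates, weeks 2 and 4 will agree more closely than weeks 2 and 24, which is the pattern that violates sphericity.

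At stake is the type I error of the longitudinal comparison between arms. The article does not merely leave the matter open: it declares the assumptions met, for a design in which one of them is doubtful.

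**Working it through.** **1. Which test do the stated numbers fit?** Inputs from Sample size: two groups, four follow-ups, effect size 0.50, alpha 0.05, totals of 47 (80%) and 62 (90%). The totals fit only if 0.50 is used as Cohen's *f*. For a within-subject term with *m* occasions, power comes from a noncentral F with

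df1 = (m−1)ε, df2 = (N−2)(m−1)ε, λ = f²Nε.

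For m = 4, ε = 1, N = 62: df = 3 and 180, λ = 0.25 × 62 = 15.5, power 0.920.

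| Test, f = 0.5 | N for 80% | N for 90% |
|---|---|---|
| Stated in the article | 47 | 62 |
| Within-subject, m = 4, ε = 1 | 45 | 59 |
| Within-subject, m = 5 (baseline counted), ε = 1 | 49 | 63 |
| Multivariate-type F, m = 4, df2 = N−4 | 48 | 61 |
| Between-group F, one measurement | 34 | 45 |

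The stated pair lies close to the within-subject rows and far from the between-group row. A within-subject term is therefore the likelier object of the calculation, and it also fits an objective worded as a difference in improvement.

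**2. What happens to type I error?** The documents give no covariance, so each pattern below is an assumption. Setting: 70 × 0.9 = 63 evaluable patients, no true difference, uncorrected group-by-time F at 5%, 8,000 simulated trials per pattern. Sphericity is measured by ε = tr(A)² / [(m−1) tr(A²)], where A is the covariance of orthonormal visit contrasts; ε = 1 means sphericity.

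Pure serial decay (correlation = ρ to the power of weeks apart):

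| ρ per week | ε, four follow-ups | Error | ε, five occasions | Error |
|---|---|---|---|---|
| 0.90 | 0.74 | 6.5% | 0.65 | 7.2% |
| 0.95 | 0.65 | 7.2% | 0.56 | 8.3% |
| 0.98 | 0.60 | 7.4% | 0.49 | 8.9% |

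Mostly exchangeable correlation (a patient-level random intercept plus noise): 5.1–5.6%.

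Across these patterns, the Greenhouse–Geisser correction brings the error to 4.4–5.1%. The between-group F stays at about 5% in every pattern tried.

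**3. Is the decay pattern compatible with the article's own correlations?** At 0.95 per week the baseline-to-24-week correlation is 0.95²⁴ = 0.29, and at 0.90 it is 0.08. Both are far below 80–90%. At 0.99 per week it is 0.99¹² = 0.89 at week 12 and 0.99²⁴ = 0.79 at week 24, in line with the article. Even so, ε for the four follow-ups is 0.57 and the error about 7.5%. High correlation is therefore no protection if the pattern is one of decay.

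**4. What does the correction cost?** At N = 62 and f = 0.5, with the arm difference in a random direction across the visit contrasts, simulated corrected power is 0.893 at ε ≈ 0.77 and 0.880 at ε ≈ 0.62. Uncorrected power is 0.921 and 0.928, bought with a type I error of 6.3% and 7.4%.

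**The case against.** The strongest reply is that a condensed article need not mention a sphericity correction. The clause about assumptions introduces the power calculation and does not rule out a check or correction in an analysis plan that is not shown. This stands in part: silence on the correction is not itself a fault, and the article never says that the F test will be uncorrected. But it does say that the assumptions are taken as met, and nothing in the text withdraws that for the analysis.

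Second, the tested term is unnamed, and a between-group F does not depend on sphericity. The planned slope, change-score and ANCOVA comparisons do not either. This also stands, and it makes the point conditional. The objective and the sample-size figures nevertheless point to a within-subject term.

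Third, serial decay is assumed. That is correct, and under near-exchangeable correlation almost nothing is lost.

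Two stronger readings are tempting and are not supported:

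- **A reader might infer that 62 patients fall short of 90% power.** The ε-scaled formula gives 72 at ε = 0.75 and 79 at ε = 0.65. But no ε is documented, and the power figure is not shown. The stated totals are also approached with five occasions at ε = 1, or with a multivariate-type F that needs no sphericity. Simulated corrected power is close to 90% anyway. Nor do the two harms occur together: uncorrected, error rises and power is kept; corrected, error is held and a little power may go.
- **A reader might take the SD rise from 0.8 to 2.4 in a cited CRFA cohort (Discussion) as evidence of non-sphericity.** That rise runs from baseline to 12 months, and the power calculation excludes baseline. Two follow-up SDs in another cited CRFA study, 2.7 and 2.8, are nearly equal. With baseline included and exchangeable follow-ups, ε is 0.92–0.97 and the error 5.0–5.1%.

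**Conclusion.** The point holds as a conditional one of modest size. If the main test is the group-by-time term, analysed by an uncorrected univariate F, and if correlation decays with time between visits, the true type I error is about 6.5–9% instead of 5%. If correlations are mostly exchangeable, it is about 5–5.6%. The documents do not settle which pattern applies. The conclusion rests on assumed covariances, 63 evaluable patients and the reading that the sized test is within-subject. It does not show that the sample size is too small. It is still worth acting on, because a method that does not depend on the doubtful assumption is readily available.

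**What to change.** 1. Name the tested term. If baseline is one of the repeated occasions, group-by-time carries the comparison of improvement. If baseline is a covariate, the between-group contrast carries it (averaged over follow-ups or at a named visit), and group-by-time only shows whether the difference changes over follow-up.
2. Replace the statement that all ANOVA assumptions are taken as met with a method that does not need sphericity: a mixed model for repeated measures on the four follow-up scores, with unstructured covariance (4 × 5 / 2 = 10 parameters) and baseline NPRS as covariate.
3. If repeated measures ANOVA is kept, pre-specify the Greenhouse–Geisser correction for every within-subject term, applied whatever a preliminary sphericity test shows.

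Cost: a sentence or two in the analysis text, fixed before unblinded data are seen, and standard functions in R, which the trial already plans to use. The downside is a small possible loss of power from the correction, to about 0.88–0.89 at 62 patients in the serial-decay cases simulated. No change to the sample size follows from this point.

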### Intervention description

#### Initial assessment

The baseline assessment will include: (a) the medical history of the patient (age, sex, body mass index, duration of pain, comorbidities, use of analgesics, and prior interventions of the knee joint); (b) radiological classification using standing AP and lateral x-rays of the knee joint and (c) baseline clinical evaluation using the NRPS, OKS, and KOOS. The OKS is a 12-item patient-reported outcome score, specifically designed and developed to assess function and pain after total knee replacement (TKR) surgery [21]. It is valid, reproducible, and sensitive to clinically important changes without a ceiling or floor effect for both its pain and function subscales [22]. The OKS has been translated and validated for Greek patients with knee osteoarthritis [23]. The KOOS questionnaire was developed in the 1990s as an instrument to assess the patient’s opinion about their knee and associated problems [24]. KOOS score has 5 subscales; Pain, other Symptoms, Function in daily living (ADL), Function in sport and recreation (Sport/Rec) and knee related Quality of life (QOL). KOOS includes WOMAC Osteoarthritis Index LK 3.0 in its complete and original format (with permission), and its convergent and divergent construct validity has been determined in multiple studies in comparison to several instruments including the different subscales of SF-36 and the Lysholm knee scoring scale [25]. The KOOS questionnaire has been translated and validated for Greek patients with total knee replacement [26].

Patients who fulfill the inclusion criteria and have no exclusion criteria will be informed about the clinical trial in detail, and a consent form will be required to proceed.

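### The main repeated measures ANOVA of NPRS is sized without the baseline score and names no baseline covariate; adjusting for the collected baseline would sharpen the arm comparison at almost no cost

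*Protocol article*

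**What the plan says.** The Initial assessment section provides for "baseline clinical evaluation using the NRPS, OKS, and KOOS", and Table 1 shows NPRS at week 0 and at 2, 4, 12 and 24 weeks.

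The Sample size section makes the difference between groups in NPRS improvement the main objective and chooses repeated measures ANOVA for it. On the inputs it says "we, as a priori, assume a number of groups equal to two and a number of measurements (except baseline) equal to four". The caption of Figure 3 likewise refers to two groups and four assessment points. The effect is described thus: "this fact denotes a medium effect size of approximately 0.50". The result is "approximately 47 patients suffice for an achieved power of 80% using rmANOVA, taking into account a moderate effect size and 62 patients for 90" percent.

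The Statistical methods section keeps this choice: "longitudinal (that is, repeated measures) analysis will be conducted with repeated measures ANOVA". It lists no model terms. Just before, it says that "the ANCOVA approach requires a significantly smaller number of participants", puts the total at 24 to 45 patients for 80% power, and calls a baseline/follow-up correlation of 0.8 to 0.9 realistic. It then uses ANCOVA for pairwise comparisons of baseline with follow-up, and for the two arms adds that "1-way ANOVA will assist in detecting variations in bivariate differences of scores".

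**The concern.** The protocol describes the gain from baseline adjustment and then sizes its main analysis without it, giving no reason. A model of the four follow-up scores alone leaves between-patient variation in starting pain in the error term. With about 35 patients per arm, the interval around the arm difference is then wider than it need be, and a moderate true difference between the two techniques is more likely to be missed. The per-visit ANCOVA does not repair this. It stands beside the longitudinal analysis, and its wording does not clearly assign it to the contrast between arms, whereas the change-score ANOVA is assigned to that contrast.

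**Working it through.** **Inputs.** From the protocol: effect size 0.50; 5% level ("Statistical significance is usually considered at the 5% level"); 1:1 allocation; 70 enrolled less 10%, so 63 evaluable; correlation ρ of 0.8 to 0.9. Assumed here: two-sided test, 0.50 read as a standardised arm difference d that is constant over the four visits, and one correlation ρ between all visits including baseline.

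**1. The protocol's own figures.**

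- ANCOVA: unadjusted total N = 4(1.960 + 0.842)²/0.5² ≈ 126. Then 126 × (1 − 0.8²) = 45.4 and 126 × (1 − 0.9²) = 23.9. This reproduces 24 to 45, with 0.50 used as d.
- Repeated measures ANOVA: noncentral F for a within-patient test, λ = f²N, df = m − 1 and (N − 2)(m − 1). With m = 4 and f = 0.50, power is 82.0% at 47 and 92.0% at 62. With f = 0.49 it is 80.2% and 90.8%. With m = 5 and f = 0.50 it is 78.1% and 89.6%.

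The printed 47 and 62 therefore fit four measurements with f slightly under 0.50, or five with f = 0.50. They do not settle whether baseline is in the model. Also, 0.50 acts as Cohen's f here and as d in the ANCOVA figure, so setting 47 beside 24 to 45 understates the gain that the protocol credits to adjustment.

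**2. Mean of the four follow-ups, without and with baseline as covariate.** In units of the single-visit variance, the variance is v0 = (1 + 3ρ)/4 without baseline and v1 = v0 − ρ² with it. The noncentrality is d/√(4v/63), on 61 or 60 df. At ρ = 0.8: v0 = 3.4/4 = 0.85 and v1 = 0.85 − 0.64 = 0.21, giving noncentralities of 2.15 and 4.33.

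| ρ | v0 | v1 | Power without | Power with |
|---|---|---|---|---|
| 0.9 | 0.925 | 0.115 | 53% | >99.9% |
| 0.8 | 0.850 | 0.210 | 56% | 99% |
| 0.5 | 0.625 | 0.375 | 70% | 89% |
| 0.33 | 0.498 | 0.389 | 79% | 88% |

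**3. Which ρ is plausible.** The Discussion cites a trial of CRFA against hyaluronic acid with NPRS 6.9 ± 0.8 at baseline and 2.8 ± 2.4 at 12 months. Reading these as standard deviations, the slope of follow-up on baseline is ρ × 2.4/0.8 = 3ρ. A slope of at most 1 (assumed) gives ρ of at most 0.33. This trial also admits only patients with NPRS of 4 or more, which narrows the baseline range. So 0.8 to 0.9 looks high.

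**4. Baseline as a fifth time level.** For a constant follow-up difference, the group-by-time noncentrality is λ = (63/4) × 0.5² × (4 − 16/5)/(1 − ρ) = 3.15/(1 − ρ), on 4 and 244 df. At ρ = 0.8, λ = 15.75 and power is 90%; at 0.9, 99.8%; at 0.5, λ = 6.3 and 48%; at 0.33, λ = 4.70 and 37%. The group main effect, diluted by the baseline visit, has 40% at ρ = 0.8.

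**5. Change score against ANCOVA at one visit.** With equal standard deviations at both times, the variances are 2(1 − ρ) and 1 − ρ². At ρ = 0.8 (0.40 against 0.36), power is 87% and 90%; at 0.9, 99.2% and 99.4%; at 0.5 (1.00 against 0.75), 50% and 62%; at 0.33 (1.34 against 0.89), 39% and 54%. The follow-up score alone has 50%.

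**The case against.** A reader might infer that the trial throws away most of its power, for instance 50% against 90% at a single visit. The documents do not support that, for several reasons.

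- **Model terms.** Excluding baseline is stated as an input to the power calculation. The analysis section does not list the terms of the repeated measures ANOVA, the objective is worded as improvement, and the printed sample sizes also fit five measurements. With baseline as a fifth level, the interaction test has 90% to 99.8% power at the protocol's own correlations. This stands as a limit on the size of the loss. It is not a full defence, since that test weakens sharply at lower correlations and gives no single arm difference.
- **The single-visit contrast.** The 50% belongs to unadjusted follow-up scores, an analysis that the protocol never names. Both of its per-visit methods use baseline, and at a correlation of 0.8 the change score loses only about 3 points to ANCOVA. This stands. The larger deficit at low correlation depends on equal standard deviations: with 0.8 and 2.4 and a slope of exactly 1, the two methods coincide. ANCOVA remains the safer choice because it estimates the slope.
- **Correlation pattern.** If follow-ups correlate more with each other (0.6, assumed) than with baseline (0.33), then v0 = 0.70, v1 = 0.70 − 0.33² = 0.59, and power rises only from 65% to 72%.
- **Effect size.** For the protocol's 2-point difference, with standard deviations of 2.4 to 2.8 taken from the cited CRFA cohorts as an assumption, d = 2/2.8 to 2/2.4 = 0.71 to 0.83. Unadjusted power is then already 83% to 94% at correlations of 0.8 to 0.9.
- **Chance imbalance.** It might also be inferred that a chance baseline difference biases the comparison. Under randomisation it does not; it is the same loss of precision, already counted above.

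**Conclusion.** The point holds as one of efficiency and clarity, not of validity. No baseline-adjusted longitudinal model is named for the main NPRS comparison, and the sizing leaves baseline out, against the protocol's own argument. Under the stated assumptions, adjustment raised power at every correlation tried. The gain is 43 points at 0.8 (56% to 99%), 19 points at 0.5 (70% to 89%) and 9 points at 0.33 (79% to 88%). The lower values deserve more weight, given the cited standard deviations, so a claim that most of the power is lost would rest on a correlation that is itself doubtful. The loss is also smaller at high correlation if baseline was intended as a fifth level, and smaller in importance for a 2-point difference. The change is worth making because it is nearly free, not because the planned test fails.

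**What to change.** In the Sample size and Statistical methods sections, define the main NPRS analysis as a longitudinal model of the scores at 2, 4, 12 and 24 weeks on arm, visit, arm-by-visit, baseline NPRS and baseline-by-visit, allowing for within-patient correlation. Report the adjusted arm differences with 95% confidence intervals. Writing out these terms also removes the doubt about how baseline enters.

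For arm comparisons at each visit (NPRS, KOOS and OKS), use ANCOVA with the baseline score of the same scale as covariate, in place of 1-way ANOVA on change scores.

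The cost is a change of wording and a few degrees of freedom. The baseline scores are already collected and standard R functions fit the model; no extra patients or visits are needed.

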In contrast to cryoneurolysis treatment, where the literature is scarce, the method of radiofrequency ablation for the treatment of symptomatic knee pain in osteoarthritic knees has been well documented in the past. In a cross-sectional survey, McCormick et al. [28] demonstrated a success rate of 35% based on a robust combination of outcome measures, and 19% of the procedures resulted in complete relief of pain at a minimum of six months of follow-up using the CRFA technique. They also demonstrated that 80% or greater relief from diagnostic blocks and a duration of pain of less than five years are associated with high accuracy in predicting treatment success. In their prospective, multicenter, randomized, crossover trial, Davis et al. [18] investigated the analgesic effect of CRFA in patients with knee osteoarthritis 12 months post-intervention and its ability to provide pain relief in patients who experienced unsatisfactory effects of intra-articular steroid injection. They demonstrated that at 12 months, 65% of the original CRFA group had pain reduction ≥ 50%, and the mean overall drop was 4.3 points (p < 0.0001) on the numeric rating scale, while 75% reported ‘improved’ effects. Hunter et al. [45] performed an extended evaluation of the patients enrolled in the study of Davis et al. [18] at 18- and 24-months post-intervention, showing a perceived positive effect with a mean NPRS score of 3.1 ± 2.7, and 3.6 ± 2.8, respectively. In another multicenter, randomized clinical trial, Chen et al. [17] compared the effectiveness of CRFA and a single injection of hyaluronic acid for the treatment of chronic knee pain; at 12-months, 65.2% of participants in the CRFA cohort reported ≥ 50% pain relief from baseline with a mean NPRS of 2.8 ± 2.4 (baseline 6.9 ± 0.8). Participants in the CRFA cohort also showed a 46.2% improvement in the total WOMAC score at the 12-month time point. Carlone et al. [46], in a recent retrospective review of 176 patients who underwent genicular nerve ablation, block, or both, found that 31.8% of the participants failed to respond to the block procedure, mainly due to the associated psychological comorbidities, smoking history, and diabetes. They also demonstrated that of the participants who underwent genicular nerve ablation, 53.7% reported less than 50% pain relief and 46.3% reported pain relief greater than or equal to 50% at the first follow-up visit.

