### Strengths and limitations

This will be a single-blinded randomized control trial with a follow-up period of six months. The strengths are the recruitment of enough patients to demonstrate a statistical significance of 90%, the precise targeting of the nerves in six different areas in accordance with old proven clinical reports and the new landmarks provided by recent anatomical studies and also that both techniques (CRFA and CRYO) would be applied at the same manner. Technical limitations also exist, as the effectiveness of these treatments relies heavily on accurate spotting of the genicular nerves and also from the fact that we are not able to spot all the nerves of the knee joint capsule. The extent of nerve damage and its capacity to regenerate also depends on parameters that cannot be fully controlled in this clinical trial. CRFA has a different mechanism of action (thermoablation with permanent? nerve damage) compared to CRYO that provokes cryoablation with Wallerian degeneration. This might reduce potential risks associated with the CRYO procedure but might also attenuate treatment effects. If CRYO turns out to be more effective or safer than CRFA would be probably considered as a novel non-pharmacological option for KOA that would be covered by medical insurances in the future.

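### The 47/62-patient sizes and 90% power are unsupported for the between-arm objective: the effect size of 0.50 comes from a fall expected in both arms

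*Protocol article*

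**What the plan says.** The Sample size section (Protocol article) gives the main objective as a comparison of NPRS improvement between the two groups, to be tested by repeated measures ANOVA with two groups and four measurements, baseline not counted. The effect-size input is that "the NPRS is expected to be reduced in the two groups (CRYO and CRFA) at least 30%, relative to baseline assessment", and the text goes on that "this fact denotes a medium effect size of approximately 0.50". It does not say whether 0.50 is Cohen's d or the ANOVA effect size f. It gives no SD, no between-arm difference and no correlation, and does not say which effect in the ANOVA is powered. The result is that "approximately 47 patients suffice for an achieved power of 80% using rmANOVA, taking into account a moderate effect size", with 62 for 90% power, raised to 70 for 10% loss.

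Two statements in Statistical methods bear on this. For ANCOVA, "a power of 80% is achieved with 24–45 patients in total", given a baseline-to-follow-up correlation of 0.8–0.9. On interpretation: "A statistically significant difference of at least two in NPRS scores between groups, will be interpreted as a minimal clinically important difference (MCID"). Strengths and limitations then claims "recruitment of enough patients to demonstrate a statistical significance of 90" per cent.

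**The concern.** The effect size answers a different question from the objective. A fall of at least 30% in each arm describes change within arms. It fits the main hypothesis in Methods, that both techniques improve on baseline, but it leaves the contrast between arms undefined. Power for that contrast needs a between-arm difference, and the plan has one: the 2 points in Statistical methods. The calculation does not use it.

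What is at stake is how a non-significant result would be read. The article presents 90% as a strength (and calls it significance rather than power). A reader could take a null comparison as good evidence that the techniques are alike, with an assurance the stated inputs do not provide.

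**Working it through.** **Inputs.** Alpha: "Statistical significance is usually considered at the 5% level" (Sample size), taken as two-sided. Two arms, 1:1 (Methods). N = 62 evaluable, 31 per arm; 70 × 0.9 = 63, which agrees. Effect size 0.50 (Sample size). Correlation 0.8–0.9 between baseline and follow-up, and the 2-point threshold (Statistical methods). Follow-up SDs of 2.4, 2.7 and 2.8 from cited CRFA cohorts at 12, 18 and 24 months (Discussion). My assumptions: compound symmetry, equal variances, and the same arm difference at every follow-up visit.

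**1. Reproducing 47 and 62.** Noncentral F with λ = f²N, df₁ = m − 1, df₂ = (N − 2)(m − 1), f = 0.50:

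| Measurements m | N for 80% | N for 90% | Power at 47 | Power at 62 |
|---|---|---|---|---|
| 5 (with baseline) | 49 | 63 | 78.1% | 89.6% |
| 4 | 45 | 59 | 82.0% | 92.0% |

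A different route, the arm effect over four visits at d = 0.50, gives exactly 47 and 62 if the between-visit correlation is about 0.14. More than one setting fits, and Fig. 3 is not shown.

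**2. Reproducing 24–45.** Unadjusted total N for d = 0.50 at 80% power is 4 × (1.960 + 0.842)² / 0.50² = 125.6. ANCOVA multiplies by 1 − ρ²:

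- ρ = 0.8: 125.6 × 0.36 = 45.2
- ρ = 0.9: 125.6 × 0.19 = 23.9
- ρ = 0.5: 125.6 × 0.75 = 94.2
- ρ = 0.3: 125.6 × 0.91 = 114.3

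The printed range is therefore built on a between-arm d of 0.50 and depends wholly on ρ of 0.8–0.9. The lower values of ρ are my assumption.

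**3. Does the 30% give 0.50?** The between-arm effect is the difference between two falls. A common floor of 30% does not fix it. Nor does 0.50 follow as a within-arm effect, since no SD is given. As an illustration from one cited trial, "with a mean NPRS of 2.8 ± 2.4 (baseline 6.9 ± 0.8"), 30% of 6.9 is 2.07 points, and 2.07 / 2.4 = 0.86.

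**4. Power at N = 62 for a between-arm d of 0.50.**

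- *One visit, unadjusted.* Noncentrality 0.50 × √(31/2) = 1.97 on 60 df: 49%. Needs 128 for 80% and 171 for 90%.
- *Arm effect, mean of four follow-ups.* d′ = 0.50 / √((1 + 3ρ)/4).
- *Group-by-time, five measurements.* Differences 0, 0.5, 0.5, 0.5, 0.5 have mean 0.4 and sum of squares 0.16 + 4 × 0.01 = 0.20, so λ = (62/4) × 0.20 / (1 − ρ) = 3.1 / (1 − ρ).
- *ANCOVA, one visit.* d′ = 0.50 / √(1 − ρ²).

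| ρ | Arm effect, four visits | Group-by-time, five measurements | ANCOVA, one visit |
|---|---|---|---|
| 0.3 | – | – | 53% |
| 0.5 | 69% | 48% | 61% |
| 0.8 | 56% | 90% | 90% |
| 0.9 | 52% | 99.7% | 99% |

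**5. Power at N = 62 for the plan's 2 points, one unadjusted visit.** SD 2.4: d = 0.83, 90%. SD 2.7: d = 0.74, 82%. SD 2.8: d = 0.71, 79%. For the arm effect over four visits, d′ = (2/SD) / √((1 + 3ρ)/4): at ρ = 0.8, 94% (SD 2.4) and 85% (SD 2.8); at ρ = 0.9, 92% and 82%.

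**The case against.** The best defence is that the figures can be met on the article's own inputs. With d = 0.50 at all follow-ups and ρ = 0.8, the five-measurement group-by-time test has λ = 3.1 / 0.2 = 15.5, which equals 0.50² × 62; power is 89.6% at 62 and 78.1% at 47. ANCOVA at ρ = 0.8 also gives about 90%. The sample is also adequate for the 2-point threshold at an SD of 2.4.

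This stands, and it rules out three stronger readings:

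- A reader might infer that 90% power is simply not achieved. The documents do not show that; it depends on the test and the correlation.
- A reader might infer that 0.50 must have been entered as f, a large effect. Step 1 shows another route, the defence above shows that f = 0.50 in that formula can match a moderate d, and Fig. 3 is not available to settle it.
- A reader might infer that the planned between-arm effect is zero. A floor of 30% does not say that the two falls are equal.

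The defence does not supply the missing justification. The Sample size section counts four measurements without baseline, and the Fig. 3 caption speaks of four assessment points. Over four post-baseline visits a constant arm difference lies in the arm effect, not the interaction, and there a correlation of 0.8–0.9 gives 56–52%. That correlation appears only under Statistical methods, for ANCOVA, introduced as another approach. The cited trial's SDs of 0.8 at baseline and 2.4 at follow-up give some reason to doubt it: the slope would be 0.8 × 2.4/0.8 = 2.4 to 0.9 × 2.4/0.8 = 2.7 follow-up points per baseline point. They come from another population, so this is a caution, not a refutation.

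**Conclusion.** The point holds as a failure of justification, not as proof of an underpowered trial. The 0.50 is taken from change within arms and says nothing about the stated between-arm objective, so neither the 47/62 sizes nor the 90% claim is supported by what is written.

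For a moderate between-arm effect, power at 62 runs from about 50% to above 99%, depending on a test and a correlation that the Sample size section does not state. That range rests on compound symmetry, a constant effect after baseline and two-sided 5%. For the plan's own 2 points, 62 patients give 79–90% at one unadjusted visit if the SD is 2.8–2.4. Those SDs come from cited cohorts at 12–24 months, later than this trial's 24 weeks. The sample of 70 can stand; its derivation cannot.

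**What to change.** Keep 70 patients and change the text.

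1. **Sample size:** delete the step from the 30% fall to 0.50 and the sizes that rest on it. State the target as a between-arm difference of 2 NPRS points, with the SD, the correlation and the effect tested. For example: assumed SD 2.4 (range to 2.8), 62 evaluable, two-sided 5%, power 90% (79%) at one unadjusted visit. Add the matching figure for the planned repeated measures or ANCOVA contrast, so that calculation and analysis agree.
2. **Smaller effects:** report power for d = 0.50 as a range over the correlation (ANCOVA at 62: 53% at 0.3, 61% at 0.5, 90% at 0.8), not as one figure.
3. **Statistical methods:** show the ANCOVA size of 24–45 as conditional on a correlation of 0.9–0.8, with 94–114 at 0.5–0.3 beside it, marked as an assumed range.
4. **Strengths and limitations:** replace the 90% significance claim with the restated power.

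The cost is rewording and one recalculation, with no extra patients. The claimed sensitivity to a moderate difference becomes conditional.
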